### ATD therapy (CBZ and PTU)

A 12-month course of ATD will be administered to induce a euthyroid state in the months following diagnosis. Therapy will normally be with CBZ, which can be administered once daily. PTU is a second-line therapy because of the increased likelihood of hepatic failure with this drug. It is proposed that CBZ dose be titrated against prevailing thyroid function tests in order to maintain a euthyroid state. Clinicians will be encouraged to follow the schedule outlined in table 1 when administering ATD to patients enrolled into this clinical trial, although the managing clinician can elect not to follow the above framework if their assessment of the overall clinical picture suggests that this is in the patients’ best interests. PTU can be administered on the basis that 5 mg of CBZ is equivalent to 50 mg PTU. If patients become hypothyroid (with an elevated TSH and low FT4/FT3 level) on the smallest daily dose of CBZ (5 mg) or PTU (50 mg), then the ATD can be administered on alternate days. If patients are still hypothyroid, then the ATD will be stopped before 12 months has elapsed following RTX therapy.

**Table 1 T1:** CBZ dose adjustment according to changing thyroid hormone status

Week/stage of trial	Thyroid hormone level: FT4 and FT3 (pmol/L)	CBZ dose (mg)
Presentation		20 mg CBZ once daily (consider 10 mg in the case of mild hyperthyroidism, FT3<10).
Week 4	Biochemically hypothyroid (low FT4, FT3 not raised).	Reduce to 5 mg.
	FT3 normal and FT4 falling.	Consider reducing from 20 mg to 10 mg, or from 10 to 5 mg.
	FT3 elevated.	Continue prior dose.
Week 8	Biochemically hypothyroid (low FT4, FT3 not raised).	Reduce to 20 mg, 10 mg, 5 mg, or reduce CBZ to 5 mg alternate days.
	FT3 normal and FT4 falling.	Reduce from 20 mg to 10 mg, from 10 mg to 5 mg, or remain on 5 mg.
	FT3 elevated but improving.	Continue prior dose.
	FT3 raised or increasing further.	Consider increasing CBZ by 10 mg daily.
Week 12 and beyond	Biochemically hypothyroid (low FT4, FT3 not raised).	Reduce to 10 mg, 5 mg or reduce CBZ to 5 mg alternate days.
	FT3 normal (or elevated with low FT4).	Continue current dose.
	FT3 elevated.	Consider increasing CBZ by 10 mg daily or 5 mg daily if previously euthyroid.
Week 16 and beyond	TSH elevation (>4 mU/L) (TSH takes precedence over thyroid hormone levels).	Reduce CBZ dose by 5–10 mg daily.
	TSH still suppressed.	Follow guide above for week 12.

CBZ, carbimazole; FT3, free tri-iodothyronine; FT4, free thyroxine; TSH, thyroid stimulating hormone.

Any participants who develop unacceptable toxicity to CBZ (notably neutropaenia with a neutrophil count less than 0.5×10^9^/L) will stop ATD immediately. Participants with a neutrophil count between 0.5 and 1.0 can remain on ATD if well. The neutrophil count should be repeated after approximately 1–2 weeks or as clinically indicated to confirm that it has not fallen to less than 0.5×10^9^/L. PTU can be commenced as a replacement ATD in the case of adverse events that do not involve hepatic dysfunction or neutropaenia. The increased risk of liver dysfunction on PTU will be discussed with participants and their families prior to commencing PTU. Patients on PTU will have liver function checked at each visit and PTU stopped if ALT or bilirubin is elevated (2× above the upper limit of normal). If patients are unable to tolerate ATD, then it may be feasible to monitor patients off treatment or manage them symptomatically with beta blockade on the basis that RTX may alter the disease natural history and result in remission without further ATD. This option can be discussed with the participant/the participant and their family. Other potential means of maintaining a euthyroid state can be discussed with the trial management team.

Patients who relapse in the second year of the trial will be encouraged to return to ATD in the first instance.

### Outcome measures

#### Primary

The number of subjects in remission at 2 years following a single dose of RTX and a 12-month course of ATD is the primary trial endpoint: this is equivalent to the number who have not relapsed. Subjects will be deemed to have relapsed if they are receiving any concomitant ATD medication in the second year post-RTX administration, or have undergone surgical (thyroidectomy) or RI treatment because of hyperthyroidism at any time following RTX administration. They will also be deemed to have relapsed if serum TSH is less than the lower limit of the normal laboratory reference range and serum FT3 is above the upper limit of the normal laboratory reference range at 2 years.

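### A patient kept euthyroid at 2 years by a treatment other than ATD, thyroidectomy or radioiodine would be counted as a remission

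*Protocol article*

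**What the plan says.** Under Outcome measures, Primary, the article counts patients in remission at 2 years and adds that "this is equivalent to the number who have not relapsed". Any patient who meets no relapse criterion is therefore a success. There are three criteria:

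- ATD in year 2: "Subjects will be deemed to have relapsed if they are receiving any concomitant ATD medication in the second year post-RTX administration".
- Definitive treatment: patients who "have undergone surgical (thyroidectomy) or RI treatment because of hyperthyroidism at any time following RTX administration".
- Biochemistry: TSH below its reference range while "serum FT3 is above the upper limit of the normal laboratory reference range at 2 years".

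The section headed ATD therapy (CBZ and PTU) deals with patients who cannot tolerate ATD. PTU may replace CBZ unless the adverse event involved the liver or neutropaenia. Otherwise the clinician may "monitor patients off treatment or manage them symptomatically with beta blockade". The paragraph closes with: "Other potential means of maintaining a euthyroid state can be discussed with the trial management team". It does not say what those means are and sets no time limit on them. A separate sentence adds: "Patients who relapse in the second year of the trial will be encouraged to return to ATD in the first instance".

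Table 2 schedules thyroid function and concomitant medication at every visit, including weeks 65, 78, 91 and 104.

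**The concern.** The two sections do not fit together. One leaves room for keeping a patient euthyroid by something other than CBZ or PTU. The other recognises treatment as relapse only if it is ATD, thyroidectomy or radioiodine. A patient whose disease is still active, and whose hormones are normal at week 104 because of a treatment outside that list, passes all three criteria and enters the numerator.

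The gap works in one direction. It can turn a non-remission into a remission but never the reverse. The decision rests on whether a small count reaches a critical number, so a single patient can matter. The trial is also open-label and single-arm, so there is no control group in which the same misclassification would occur and partly cancel.

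**Working it through.** **Step 1: does any criterion catch the patient?** Take a patient who stopped CBZ for neutropaenia, so that the article does not offer PTU as a replacement. In year 2 the patient is kept euthyroid by another means agreed with the trial management team, and FT3 is in range at week 104.

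| Criterion | Met? |
|---|---|
| ATD in year 2 | No, if ATD means CBZ or PTU, as in the section heading and the inclusion criteria |
| Thyroidectomy or radioiodine | No, unless the other means was one of these |
| Low TSH with high FT3 at 2 years | No, FT3 is in range |

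No criterion is met, so the patient counts as a remission.

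**Step 2: which of the named options open the gap?** Monitoring off treatment does not: a patient who is euthyroid at 2 years without treatment is in remission. Beta blockade is described as symptomatic ("manage them symptomatically with beta blockade"), so a patient on it with low TSH and high FT3 at week 104 is still a relapse. Only the unnamed other means remain.

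**Step 3: reproduce the design.** Inputs from Sample size: unacceptable rate 20%, desired rate 40%, alpha 10%, power 80%, 10% loss to follow-up. The critical number is not published. An exact binomial search for the smallest n with P(X ≥ r | 0.20) ≤ 0.10 and P(X ≥ r | 0.40) ≥ 0.80 gives n = 24, r = 8:

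- P(Bin(24, 0.20) ≥ 8) = 0.0892
- P(Bin(24, 0.40) ≥ 8) = 0.8081
- 24 / 0.9 = 26.7, rounded up to 27, which is the stated target.

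**Step 4: illustrate one miscount (assumed rule: 8 of 24).** Suppose one of the 24 is a true non-remitter who is certain to be scored as a remission. The other 23 remit with probability 0.20, and 7 more remissions suffice:

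- P(Bin(23, 0.20) ≥ 7) = 0.160, against the design value of 0.089.
- Scored correctly, the same 24 patients would give P(Bin(23, 0.20) ≥ 8) = 0.072.

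If all 27 were evaluable under an assumed rule of 9 of 27, the design value would be 0.074, and one certain miscount would give P(Bin(26, 0.20) ≥ 8) = 0.131.

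**Step 5: illustrate a rate.** Let q be the assumed share of true non-remitters scored as remissions. At a true rate of 20% the apparent rate is 0.20 + 0.80q.

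| q | Apparent rate | P(proceed), 8 of 24 | P(proceed), 9 of 27 |
|---|---|---|---|
| 0 | 0.200 | 0.089 | 0.074 |
| 2% | 0.216 | 0.127 | 0.109 |
| 5% | 0.240 | 0.199 | 0.179 |

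The document gives no value for q. The table shows how little slack the rule has; it does not estimate the error.

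**The case against.** **The other means may already be covered.** The sentence names no treatment and authorises none. It may simply point to surgery or radioiodine, which count at any time, and the Discussion foresees definitive treatment when ATD has to be stopped. It is also arguable that the phrase about any ATD medication reaches beyond CBZ and PTU, since the abstract says only that the drug is usually carbimazole. This stands as a limit on how many patients are affected. It does not remove the gap, because the text does not confine the other means to treatments that are counted. If the sponsor intends that, one line would settle it.

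**The definition is not lenient throughout.** Any ATD in year 2 counts as relapse without a biochemical requirement, so some patients may be scored as failures on treatment alone. That is correct, but it does not offset this particular error in any known proportion.

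**Year-2 biochemistry.** A reader might infer that high FT3 at week 65, 78 or 91 should also count as relapse in the primary endpoint, because return to ATD is only encouraged. The document does not support going that far. The endpoint and the 20% and 40% benchmarks refer to remission at 2 years, and reading biochemistry at that visit matches them. Counting earlier episodes would score late remission without further treatment as failure. The interim results are also not lost: Analysis of secondary outcome measures reports the proportion of time TSH, FT4 and FT3 are in range between stopping ATD and trial end.

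**Number at risk.** A reader might take the 20% CBZ adverse-event figure in the Introduction as about 5 of 27 patients exposed (27 × 0.20 = 5.4). That figure covers all adverse events, including minor ones, and is not a rate of stopping ATD; many such patients could change to PTU.

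**Conclusion.** The point holds in a narrow form. As written, the primary endpoint counts as a remission a patient who is in range at week 104 only through a treatment other than ATD, thyroidectomy or radioiodine, and the ATD section leaves room for such a patient. The error can only favour proceeding.

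This rests on reading ATD as CBZ and PTU, and on the other means including something beyond surgery or radioiodine. The number affected is probably small and cannot be derived from the document. The rise from 8.9% to 16.0% assumes both the 8-of-24 rule and one certain miscount; it must not be read as the trial's actual type I error. The sample size itself reproduces and is not in question.

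**What to change.** Reconcile the two sections on how these patients are classified. For the primary analysis, widen the first relapse criterion to *ATD or any other treatment given to lower thyroid hormone levels in the second year*, taken from the concomitant medication recorded at weeks 65, 78, 91 and 104. Beta blockade, described as symptomatic, would stay outside this wording, and the biochemical criterion still covers those patients at 2 years.

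Keep the biochemical criterion at 2 years in the primary endpoint. Applying it at weeks 65, 78 and 91 should be at most a sensitivity analysis.

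The cost is a change of wording in the endpoint definition and the analysis plan. No visit, sample or patient is added, and the care of patients does not change. The one downside is that the observed remission rate may be slightly lower.

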### Inclusion criteria

Excess thyroid hormone concentrations at diagnosis: elevated free FT3 and/or FT4 (based on local assay).Suppressed (unrecordable) TSH (based on local assay).Patients between the ages of 12 and 20 years inclusive who are less than 6 weeks from the initiation of ATD treatment (CBZ or propylthiouracil [PTU]) for the first time.Elevated thyroid binding inhibitory immunoglobulin or thyroid receptor antibodies (TRAb including thyroid binding inhibiting immunoglobulin [TBII]) based on local assay. Patients may or may not have a raised thyroid peroxidase antibody titre.All patients must be willing to use effective forms of contraception for 12 months post-treatment with RTX.If women are of childbearing potential, they must have a negative pregnancy test at screening. This will need to be repeated on the day of RTX administration if more than 7 days has elapsed since the screening visit or a negative pregnancy test.Able and willing to adhere to a 2-year trial period.

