### Visit details and assessments

Following screening and consent, RTX is administered at the baseline visit (week 0). Subsequent visits are scheduled until 24 months; the details are provided in table 2. In addition, after each visit in the first 12 months, participants are contacted by telephone to document changes in ATD dosages. Calls should be completed within 10 days of the visit.

**Table 2 T2:** Schedule of events

Assessments/Intervention	Trial period														
	Screening/Consent	Trial intervention	Follow-up												
	Week −6 to 0	0	4	8	12	16	20	28	36	44	52	65	78	91	104
Confirmation of eligibility	X	X													
Informed consent and assent	X														
HBsAg, HB Core and HCV antibodies	X														
Pregnancy test (women)	X	X									X				
Medical history		X													
Clinical examination		X	X	X	X	X	X	X	X	X	X	X	X	X	X
Height		X						X			X		X		X
Weight		X	X	X	X	X	X	X	X	X	X	X	X	X	X
RTX infusion		X													
ATD regimen		X	X	X	X	X	X	X	X	X	X				
ATD compliance			X	X	X	X	X	X	X	X	X				
Concomitant medication		X	X	X	X	X	X	X	X	X	X	X	X	X	X
Adverse and serious adverse event		X	X	X	X	X	X	X	X	X	X	X	X	X	X
Thyroid function (TSH, FT4 and FT3)		X	X	X	X	X	X	X	X	X	X	X	X	X	X
Liver function (ALT and bilirubin) if on PTU		X	X	X	X	X	X	X	X	X	X	X	X	X	X
Thyroid antibodies (TRAB and TPO)		X			X			X	X		X				X
Lymphocyte subsets*		X	X		X			X	X		X				X
Full blood count		X	X		X			X	X		X				X
Immunoglobulin levels (IgG, IgM, IgA)		X			X			X	X		X				X
Specific antibody levels (tetanus, Hib, pneumococcus)		X									X				X
Thyroid function (TSH, FT4 and FT3)—central analysis		X									X				X
Serum for exploratory analyses		X									X				X

ATD dose is adjusted at each visit if required.

*Lymphocyte subsets: T cells (CD3), helper T cells (CD4), cytotoxic T cells (CD8), B cells (CD19) and class switch B cells (CD27+ IgD−).

ALT, alanine transaminase; ATD, antithyroid drug; FT3, free tri-iodothyronine; FT4, free thyroxine; HB Core, hepatitis ‘B’ Core antibody; HBsAg, hepatitis ‘B’ surface antigen; HCV, hepatitis ‘C’ virus antibody; Hib, haemophilus influenzae type B; PTU, propylthiouracil; RTX, rituximab; TPO, thyroid peroxidase; TRAb, thyrotropin receptor antibody; TSH, thyroid stimulating hormone.

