HBsAg, HB Core antibody and HCV antibody status is checked at screening/consent to establish hepatitis status to determine if the patient can be entered into the trial. A full blood count is conducted to look for evidence of change in white cell number (a recognised side effect of ATD). Lymphocyte subsets including T cells (CD3+), helper T cells (CD4+), cytotoxic T cells (CD8+), B cells (CD19+) and class switch B cells (CD27+ IgD−) and serum immunoglobulin (Ig) levels (IgG, IgM, IgA) are measured to look at the impact of RTX (anti-B cell MAb) on B and T cell populations and immunoglobulin levels (produced by plasma cells that differentiate from B cells).

Specific vaccine antibodies (against tetanus, haemophilus influenzae type B and pneumococcus) are assessed at baseline and at 12 and 24 months to look for evidence of falling levels as a consequence of the intervention.

At each visit, concomitant medications are recorded, an adverse event check is performed and thyroid function (TSH, FT4 and FT3) is assessed.

We plan to undertake exploratory analyses of immune system function on blood samples obtained prior to the RTX infusion at baseline and then after 12 months and 24 months. This will include measurement of a range of novel factors involved in immune system activity, including B lymphocyte activating factor, a proliferating-inducing ligand and B lymphocyte chemoattractant (CXCL13). These data will be analysed separately from the main trial.

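### The 2-year biochemical relapse rule ignores FT4, so an untreated patient with low TSH and raised FT4 alone is scored as a remission: a narrow gap, but one that can only add remissions

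*Protocol article*

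**What the plan says.** **Endpoint (Protocol article, Outcome measures, Primary).** The endpoint is the number in remission at 2 years, and "this is equivalent to the number who have not relapsed". There are three ways to relapse:

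- "receiving any concomitant ATD medication in the second year post-RTX administration";
- to "have undergone surgical (thyroidectomy) or RI treatment because of hyperthyroidism at any time following RTX administration";
- at 2 years, "serum TSH is less than the lower limit of the normal laboratory reference range and serum FT3 is above the upper limit" of the reference range.

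**Entry (Inclusion criteria).** The hormone criterion is "Excess thyroid hormone concentrations at diagnosis: elevated free FT3 and/or FT4 (based on local assay"), so raised FT4 alone is enough. Entry also needs "Suppressed (unrecordable) TSH (based on local assay") and a raised TSH-receptor antibody.

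**Measurement (Visit details and assessments).** At each visit "thyroid function (TSH, FT4 and FT3) is assessed". Table 2 lists all three tests locally at every visit from week 0 to week 104, and centrally at weeks 0, 52 and 104.

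**Decision rule (Sample size; Analysis of the primary outcome measure).** The count in remission is compared with a critical number, set from remission rates of 20% (unacceptable) and 40% (desired), alpha 10% and beta 20%. The target is 27 patients, allowing for 10% loss to follow-up. The critical number itself is held in the statistics trial master file and is not given.

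**The concern.** Remission is defined only as the absence of relapse, so any hyperthyroid state that the relapse criteria miss becomes a success. Raised FT4 with in-range FT3 is such a state. The trial accepts that hormone pattern as thyroid hormone excess at entry, and the article gives no reason for treating it differently at the end.

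The omission cannot turn a remission into a relapse; it can only work the other way. There is no control arm in which the same scoring would apply and offset it, and the benchmarks of 20% and 40% are fixed rates. The decision turns on a count of about eight, so a single misclassified patient could tip it towards a randomised trial. FT4 also belongs to the trial's own description of thyroid status in year 2 (Analysis of secondary outcome measures). The same patient could therefore be abnormal there and a success in the primary analysis.

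**Working it through.** **1. Which patient falls through.** Take a patient at week 104 with TSH below range, FT4 above range and FT3 in range.

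| Relapse criterion | Met? |
|---|---|
| Any ATD in year 2 | Only if treatment was restarted or continued |
| Thyroidectomy or radioiodine for hyperthyroidism | Only if performed |
| Low TSH and raised FT3 at 2 years | No, FT3 is in range |

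If the first two are not met, the patient is scored a remission. Being off ATD at week 104 is not sufficient; there must have been no ATD at any time in year 2.

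**2. Reproduce the design.** Inputs from Sample size: p0 = 0.20, p1 = 0.40, alpha 0.10, power 0.80, 10% loss. The smallest n for which some r gives P(X ≥ r | n, 0.20) ≤ 0.10 and P(X ≥ r | n, 0.40) ≥ 0.80 is n = 24 with r = 8:

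- P(X ≥ 8 | 24, 0.20) = 0.0892
- P(X ≥ 8 | 24, 0.40) = 0.8081
- 24 / 0.9 = 26.7, rounded up to 27

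This agrees with the stated 27. The critical number of 8 is derived here, not disclosed. If all 27 are evaluable, the corresponding cut-off is 9 (alpha 0.0737, power 0.8161).

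**3. Effect of misclassification.** Let m be the share of true non-remitters scored as remissions through this gap. The documents give no value, so m is an assumption and is shown as a range. The apparent remission rate at 20% true remission is q = 0.20 + 0.80 × m, and the chance of proceeding is P(X ≥ r | n, q).

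| m | q | 8 of 24 | 9 of 27 |
|---|---|---|---|
| 0 | 0.200 | 8.9% | 7.4% |
| 0.5% | 0.204 | 9.8% | 8.2% |
| 1% | 0.208 | 10.7% | 9.0% |
| 2.5% | 0.220 | 13.8% | 12.0% |
| 5% | 0.240 | 19.9% | 17.9% |

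With 8 of 24, the 10% alpha is passed at m of about 0.6%; with 9 of 27, at about 1.5%. For scale, 24 patients at 20% true remission include 24 × 0.80 = 19.2 non-remitters, so m = 5% means 19.2 × 0.05 = 0.96, about one patient on average, and m = 1% means about 0.2.

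**4. One misclassified patient.** If one of the 24 is certain to be a false remission, the other 23 need only 7: P(X ≥ 7 | 23, 0.20) = 16.0%. This supposes that the error has already happened, so it shows sensitivity to one patient and is not the error rate of the design.

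**The case against.** **The treatment criteria close most of the gap.** Thyroid function is checked at weeks 65, 78, 91 and 104, patients who relapse in year 2 are encouraged to return to ATD, and any ATD in that year counts as relapse. This stands. A reader might infer that a patient who entered on raised FT4 alone could easily finish with unchanged biochemistry and be a success. That would need hyperthyroidism to go untreated through all the year-2 visits, or to appear first around week 104. The gap remains because return to ATD is encouraged and not required, and because a patient first found abnormal at week 104 has no later visit.

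**FT3 may have been chosen on purpose.** In Table 1, mild disease is graded by FT3, the rows for raised hormone rest on FT3, and no row acts on a raised FT4. This is a fair argument for intent. But the table guides dose adjustment and does not define freedom from disease, and the article does not offer it as the reason.

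**Entry and relapse criteria need not be identical.** This is also correct. They differ elsewhere: entry needs unrecordable TSH and a raised antibody, while relapse needs only TSH below range. So the two sections do not contradict each other outright, and adding FT4 would align only the hormone part.

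**The size is unknown.** With 8 of 24, the false-go rate stays under 10% for m below about 0.6%; with 9 of 27 it is still 9.0% at m = 1%.

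**FT4 abnormality would be visible elsewhere.** The secondary analysis describes all three hormones in each patient during year 2. That exposes the problem but does not change the count on which the decision rests.

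**Conclusion.** The point holds in a limited form. As written, the rule scores as a remission a patient with low TSH, raised FT4 and in-range FT3 at 2 years who had no year-2 ATD and no surgery or radioiodine for hyperthyroidism. This follows from the stated endpoint, so it is not a detail left to another document. The direction is certain: the gap can only add remissions.

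The size is not established. On the assumed range of 0.5% to 5% of true non-remitters, the chance of proceeding at 20% true remission runs from 9.8% to 19.9% (8 of 24), or from 8.2% to 17.9% (9 of 27), against 8.9% and 7.4% with correct scoring. These figures rest on a derived critical number and on 20% and 40% referring to true remission. A reader might conclude that the type I error is shown to exceed 10%; the documents do not support that, because they give no frequency for FT4-only hyperthyroidism. Severity is moderate to minor.

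**What to change.** In the primary outcome definition, score biochemical relapse at 2 years as TSH below the reference range together with FT3 and/or FT4 above it, and carry the same wording into the analysis plan. This reconciles the endpoint with the hormone part of the inclusion criteria; the TSH threshold and the antibody requirement would still differ. Make the change before any week-104 results are examined.

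If the FT3-only rule is deliberate, keep it, state the reason, and prespecify a sensitivity analysis that reports the remission count under the FT3-and/or-FT4 definition.

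The cost is one phrase. FT4 is already measured at week 104, so no new data are needed, and the design stays at 24 evaluable patients and 27 recruited. The remission count may come out slightly lower. The change concerns scoring of the endpoint only, not how patients are managed.
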